### Research Design: Indigenist Methodologies

Indigenist research methodologies offer beneficial processes for research design, engagement, and facilitation for Indigenous peoples and researchers [109]. In Australia, the concept of Indigenist research emerged as a collaborative effort between Indigenous researchers and communities. Promoting self-determination, decolonization, and liberation from colonial oppression, the interconnected principles of resistance, political integrity, and prioritizing Indigenous voices are foundational principles of Indigenist research [110]. Indigenist approaches emphasize support for Aboriginal worldviews, knowledge systems, and social norms taking precedence in research, helping to ensure Indigenous perspectives are not subordinated to Western research standards [111]. Internationally, Indigenist methodologies with similar interpretations and applications have been endorsed by numerous Indigenous and First Nations scholars [112-115]. Through Indigenist research, emphasis is placed on equitable involvement of all peoples. This enables Indigenous communities to meaningfully contribute toward decision-making, governance, and leadership across all research components [116-119]. Indigenist methodologies were chosen as the most suitable methodological approach to inform our research design. This respects and enacts self-determination for Tribal Warrior and Aboriginal community members within this study. Our Indigenist research design will ensure the VR application is co-designed and codeveloped from a culturally centered positionality. Qualitative findings and iterative co-design outcomes will inform VR application content codevelopment, prioritizing cultural knowledges, lived experiences, SEWB, and CDH support needs. Our use of Indigenist methodologies will ensure that the work of USYD researchers, Studio Gilay, and Phoria is responsive to self-determined decisions made by Tribal Warrior. This governance and leadership commitment will enable the partnership to align VR application co-design and codevelopment with how Tribal Warrior provides SEWB and CDH support for the local Aboriginal community. A visual overview of how Indigenist methodologies inform the research design is provided, as (Figure 3) shows:

**Figure 3. F3:**
[figure not shown]
Research facilitation—participatory action research methodology. USYD: University of Sydney; VR: virtual reality.

### Research Facilitation: PAR Methodology

PAR methodologies emphasize the central role of research participants. PAR promotes that consistent and equitable participant involvement across all components of research is necessary for ethical, sustainable, and impactful research [120-122]. This requires the prioritization of forming practical partnership dynamics, having relational accountability, and consistently communicating progress or challenges with all involved in the research. PAR processes operate cyclically, encompassing reflection, planning, action, observation, and subsequent action. For participants, this means consistently providing leadership and governance, aiming to produce relevant and beneficial outcomes of importance to participant needs and contexts [123]. PAR expects that all stakeholder perspectives are valued equally across all components of research [124,125]. For research aiming to explore, comprehend, and define potential improvements with specific people and contexts, PAR is recognized as a suitable methodology. Furthermore, PAR has been identified as an effective method for conducting research with Aboriginal, Indigenous, and First Nations peoples. Several successful applications of PAR have been documented across various health and wellbeing projects involving Aboriginal, Indigenous, and First Nations peoples [126-138]. PAR methodologies will inform research facilitation of this study, ensuring Tribal Warrior staff and Aboriginal community members are involved across all components of research. For Tribal Warrior, our PAR approach will ensure all research planning, facilitation, co-design, and codevelopment of VR application content will occur based on constant communication, integration of feedback, and shared decision-making. The use of our PAR approach for research facilitation will uphold respect for the expertise of Tribal Warrior, an ACCO with longstanding expertise in supporting SEWB and CDH of the local Aboriginal community. Additionally, our PAR approach will assist the integration of SEWB and CDH support into the VR application, based on the lived experiences and perspectives of Aboriginal community members. A visual overview of how PAR methodologies inform the research facilitation is provided, as shown in (Figure 4):

**Figure 4. F4:**
[figure not shown]
Research design–indigenist methodologies. CDH: cultural determinants of health; SEWB: social and emotional wellbeing; VR: virtual reality.

## Methods

### Study Design

This study design includes a 3-phase mixed-methods co-design approach: phase 1 is regarding scoping; phase 2 is regarding co-design; and phase 3 is regarding implementation and evaluation. Participants will include 35 Tribal Warrior staff and/or Aboriginal community members. Qualitative yarning circles will generate data in each phase. Phase 1 thematic findings will guide iterative VR application co-design and codevelopment meetings before phase 2. Cultural knowledges, sociocultural lived experiences, SEWB, and CDH support the needs of the Aboriginal community and will inform the content of the VR application. Phase 2 will provide participants with opportunities to assess and give feedback on low-fidelity digital assets of the VR application. Thematic findings and further iterative co-design meetings will enable the redesign of content to be included in the fully developed VR application. Phase 3 will involve mixed-methods cultural relevance, acceptability, and feasibility assessment of the VR application.

### Co-Design and Codevelopment of the VR Application

Figure 5 shows how we codevelop the VR application. Our partnership will use an iterative co-design process. Phase 1 of qualitative findings will inform each co-design activity, ensuring participant evidence guides integration of cultural, SEWB, and CDH content. Findings from phase 1 will be reviewed during partnership knowledge translation meetings. Phoria will support Tribal Warrior to understand how certain VR affordances and modalities could be used to codevelop specific content conducive to providing SEWB and CDH support. Low-fidelity digital assets will then be codeveloped by Phoria, based on knowledge translation outcomes provided by Tribal Warrior. These will include concept art, storyboards, and journey-mapping outputs. Integration of feedback on content will occur until approval to proceed with VR application codevelopment is provided by Tribal Warrior. At this point, the VR application concept, content, SEWB, and CDH support experiences will be finalized. Phase 2 will generate feedback on these outputs, as well as exploring potential implementation and use case scenarios for the VR application. Repeating the above iterative co-design process, evidence will be integrated into the codevelopment of the VR application, led by Phoria and Studio Gilay. Regular partnership knowledge translation meetings will ensure codevelopment of content aligns with evidence from phases 1 and 2 and the direction provided by Tribal Warrior. Upon availability of the fully developed VR application, phase 3 will generate mixed-methods evidence of cultural relevance, acceptability, and feasibility. A visual overview of this theoretical approach is provided in the logic model, as Figure 5 shows :

**Figure 5. F5:**
[figure not shown]
Virtual reality application co-design and codevelopment process. CDH: cultural determinants of health; SEWB: social and emotional wellbeing; VR: virtual reality.

### Data Collection: Mixed Methods

Qualitative data collection will occur through yarning circles in each phase. Yarning is a culturally specific qualitative research method often used when working with Aboriginal peoples [139]. As a semistructured and circuitous research method, yarning helps to facilitate supportive relational and communication processes between Aboriginal research participants and researchers [140]. Through yarning, Aboriginal research participants are supported within culturally safe and strengths-based data collection environments. Having these environments assists participants in sharing subjective cultural knowledge and lived experiences of relevance to the research [141]. Yarning involves 4 interdependent phases of relationality and communication (social yarning, research yarning, therapeutic yarning, and collaborative yarning), which concurrently support meaningful research engagements and data collection [142]. Due to our participants being Tribal Warrior staff or Aboriginal community members, the method of yarning circles was selected.

Aboriginal researchers (JG and MD) from the USYD will lead facilitation of yarning circles, as they have expertise with this research method. Non-Indigenous staff from Phoria (JP), responsible for leading co-design and codevelopment of the VR application, will be involved through observation during phase 1 and 2 data to ensure the VR technological, design, and implementation support needs of Tribal Warrior are integrated into iterative co-design activities. At least 1 Aboriginal researcher, 1 male, and 1 female, will be present during data collection, to uphold gendered and cultural representation. Yarning circles will be approximately 2 hours for each phase, taking place on campus at the USYD, at the office of Tribal Warrior, or at a location in the local Aboriginal community deemed suitable by Tribal Warrior. Audio recordings of each yarning circle will be transcribed using a professional and confidential academic service.

Quantitative data will be collected in phase 3 to generate evidence about the cultural relevance, acceptability, and feasibility of the VR application. Collecting quantitative data through the phase 3 survey provides an opportunity to capture perspectives of individual participants regarding cultural relevance, acceptability, and feasibility of the VR application. REDCap (Research Electronic Data Capture; Vanderbilt University) software will be used to design the survey, collect data, and perform analysis [143]. Participants will complete the survey on iPads (Apple Inc), laptops, or mobile phones. The results will be presented using a summary table in the phase 3 paper. The phase 3 survey questions and associations to cultural relevance, acceptability, and feasibility are provided below, as Table 2 shows:

**Table 2. T2:** Phase 3 survey questions.

Questions	Characteristics
Question 1: what is your age? (years)	13‐24 25‐34 35‐44 45‐54 55‐64 65‐74 75 and older
Question 2 is regarding acceptability and feasibility: do you think the VR^a^ application could be used as an effective SEWB^b^ and CDH^c^ support for Aboriginal peoples?	Yes Unsure No
Question 3 is regarding cultural relevance: from the list below, which SEWB domains did the VR application explore?	Connection to country and land Connection to culture Connection to spirit, spirituality, and ancestors Connection body and behaviors Connection to mind and emotions Connection to family and kinship Connection to community
Question 4 is regarding cultural relevance: from the list below, which CDH domains did the VR application explore?	Family, kinship, and community Indigenous beliefs and knowledges Cultural expression and continuity Indigenous language Self-determination and leadership Connection to country
Question 5 is regarding acceptability and feasibility: from the list below, in which contexts do you think the VR application could be used to provide SEWB and CDH support for Aboriginal peoples?	Personal use at home Aboriginal community-controlled organizations Aboriginal medical services Mental health services Virtual therapy Hospitals/emergency departments Rehabilitation programs Youth justice or prisons Schools or universities Professional workplaces Cultural competency training Online social spaces Other: (free text entry)

a VR: virtual reality.

b SEWB: social and emotional wellbeing.

c CDH: cultural determinants of health.

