### Data Analysis, Rigor, and Handling

Data analysis will be led by USYD researchers. The reflexive thematic analysis by Braun and Clarke [144] will guide qualitative data analysis. Inductive analysis will be used for each yarning circle transcript [145]. A total of 2 Aboriginal and 2 non-Indigenous researchers will undertake preliminary open-ended coding of 2 transcripts. Collaborative yarning meetings will review preliminary findings, assessing similarities and differences in coding outcomes from all 4 researchers [146]. Any disagreements or differences resulting from reflexive thematic analysis will be resolved during collaborative yarning meetings. Upon agreement on preliminary coding and analysis insights, broader themes will be established to guide further analysis. Further data analysis will then be conducted by researchers using NVivo software (version 15; Lumivero) [147]. The lead researcher (JG) will continue with reflexive thematic analysis for each transcript, based on the themes established in collaborative yarning meetings. At least 1 other researcher will be involved in the analysis of all transcripts. When analysis of each phase is complete, USYD researchers will engage in knowledge translation meetings with Tribal Warrior, Studio Gilay, and Phoria staff. As part of the iterative co-design process, findings will be used to support Tribal Warrior with co-designing and codevelopment of VR application content. Participants will be provided with 1-page plain English summaries of findings when findings are shared in academic papers.

In phase 3, descriptive statistics analysis will be used to summarize frequencies (n) and percentages (%) of participant responses to each survey question and response option [148]. Analysis and interpretation of survey data will provide cultural relevance, acceptability, and feasibility evidence. Cultural relevance will be assessed through questions 3 and 4, quantifying participant perspectives on which SEWB and CDH domains were engaged with through the VR application experience. Acceptability and feasibility will be assessed through questions 2 and 5, quantifying whether participants accept that the VR application could be used to provide SEWB and CDH support, and in which contexts this could feasibly occur.

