### Recruitment and Sampling

Purposive sampling will be used, aiming to recruit the same 35 participants for each phase [149]. It may be necessary to recruit different Tribal Warrior staff and/or Aboriginal community member participants across phases, due to organizational changes and the unavailability of Aboriginal community members. However, all participants who become involved in this study will receive invitations to participate in future phases of data collection. Dropouts across phases will not negatively influence data collection, as involvement of different participants will increase the diversity of knowledge, perspectives, and lived experiences shared during data collection. Tribal Warrior will make self-determined decisions on which participants are recruited in each phase. All communication and engagement with potential participants will be managed by Tribal Warrior. This approach enacts self-determination and allows existing community connections and networks to be used effectively for recruitment. The sample size was selected intentionally, with Tribal Warrior confirming this approach would not be burdensome, enabling approximately one-third of all Tribal Warrior staff to be involved. Logistically, this sample size permits each yarning circle to involve 4 participants, using 4 VR headsets, in a timely yet meaningful manner. Further, this sample size aligns with previous Aboriginal wellbeing qualitative research conducted by the authors and across other Aboriginal wellbeing studies. Participant eligibility includes being a Tribal Warrior staff member and/or identifying as an Aboriginal community member. Diversity among participants will be prioritized, aiming to include representatives from each Tribal Warrior support program team and Aboriginal community members from differing cultural communities, lived experiences, ages, and genders. Ineligibility for our research includes being younger than 13 years of age [150], due to current health and safety advice on ethical use of VR hardware for young people and children. Upon confirmation of participants by Tribal Warrior, USYD researchers will provide plain English 1-page documents outlining each phase of research, how to become involved, and who to contact from the research team for further information. Upon confirmation, USYD researchers and Tribal Warrior staff will communicate details on expectations, timing, location, and phase-specific details. In each phase, participants will receive an Aus $200 (a currency exchange rate of Aus $1 = US $0.71 was applicable) visa-gift card for their time and contributions.

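### Questions 3 and 4, the only survey items for cultural relevance, offer no 'none' or 'unsure' answer, so a blank cannot be interpreted; Question 5 shares the gap to a lesser degree

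*Protocol article*

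**What the plan says.** Table 2 (Data Collection: Mixed Methods) sets out five survey questions with their answer options.

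- Question 2 asks whether the application could be an effective support. Its options are Yes, Unsure and No.
- Question 3 asks "from the list below, which SEWB domains did the VR application explore" and lists 7 domains.
- Question 4 asks "from the list below, which CDH domains did the VR application explore" and lists 6 domains.
- Question 5 asks about settings ("Question 5 is regarding acceptability and feasibility: from the list below, in which contexts do you think the VR application could be used") and lists 12 contexts. The list ends with "Online social spaces Other: (free text entry)".

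No option for 'none' or 'unsure' is printed for Questions 3, 4 or 5. Questions 3 and 4 have no free-text entry either.

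Data Analysis, Rigor, and Handling assigns the items to constructs: "Cultural relevance will be assessed through questions 3 and 4", and "Acceptability and feasibility will be assessed through questions 2 and 5". The analysis is descriptive and will "summarize frequencies (n) and percentages (%) of participant responses to each survey question and response option". The planned size is 35 (Recruitment and Sampling: "Purposive sampling will be used, aiming to recruit the same 35 participants for each phase").

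The section VR and Culturally Centered Wellbeing Support frames cultural relevance as a question of whether the content aligns with the domains. Phase 3 data collection is planned for June 2026 (Results, Overview).

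**The concern.** A question that asks whether content aligns with a set of domains needs an answer for the case that it does not. Questions 3 and 4 have none. A participant for whom no domain came through, or who could not tell, must either leave the item empty or tick something they do not hold. If blanks are allowed, 'none', 'unsure' and 'skipped' all arrive as the same empty record. If an answer is required, the only exits are positive ones.

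This is a gap in the form, so it cannot be left to an analysis plan: no later rule can recover an answer that was never offered. Condensation for the article is also an unlikely explanation, because the same table prints Unsure and No for Question 2.

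At stake is the survey's evidence on cultural relevance, which rests on these two items alone. The article justifies the survey as the means of hearing from participants individually. The group discussions in phase 3 therefore do not fully replace it.

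**Working it through.** The plan gives no figure to reproduce: there is no threshold, test or sample-size formula behind these items. The check has two parts.

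**1. What each item can record (from Table 2)**

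| Item | Construct | Listed options | 'None' or 'No' | 'Unsure' | Free text |
|---|---|---|---|---|---|
| Question 2 | Acceptability, feasibility | 3 | yes | yes | no |
| Question 3 | Cultural relevance | 7 domains | no | no | no |
| Question 4 | Cultural relevance | 6 domains | no | no | no |
| Question 5 | Acceptability, feasibility | 12 contexts plus *Other* | no | no | yes |

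Cultural relevance has no item on which absence or doubt can be stated. Acceptability and feasibility have Question 2 for that purpose, and the free text of Question 5 as a second route. The gap is therefore largest for Questions 3 and 4.

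**2. How much the ambiguity could move a percentage**

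Input from the document: N = 35. Assumed, because the document gives no such counts: k ticks for one option and b blanks on the item. It is also assumed that participants may tick several options and may leave an item blank. The plural wording suggests the first; the article states neither.

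- Blanks kept in the base: k / 35
- Blanks dropped: k / (35 − b)

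| Blanks b | k = 20, kept | k = 20, dropped | k = 25, kept | k = 25, dropped |
|---|---|---|---|---|
| 0 | 57.1% | 57.1% | 71.4% | 71.4% |
| 3 | 57.1% | 20/32 = 62.5% | 71.4% | 25/32 = 78.1% |
| 5 | 57.1% | 20/30 = 66.7% | 71.4% | 25/30 = 83.3% |
| 7 | 57.1% | 20/28 = 71.4% | 71.4% | 25/28 = 89.3% |
| 10 | 57.1% | 20/25 = 80.0% | 71.4% | 25/25 = 100% |

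Which column is right depends on what the blanks mean. Take k = 20 and b = 5, and let x of the 5 blanks mean 'none' or 'unsure' and the rest be skipped items. The share among those who really answered is 20 / (30 + x):

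- x = 0: 20/30 = 66.7%
- x = 2: 20/32 = 62.5%
- x = 5: 20/35 = 57.1%

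The form does not record x, so the data could not choose within that range. With explicit *None of these* and *Unsure* options, x is observed.

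**The case against.** **Negative views have other outlets.** Question 2 takes No and Unsure, Question 5 has free text, and phase 3 includes yarning circles. This stands, so it would be wrong to infer that the study cannot record negative views at all. It also weakens the point for Question 5: a blank from someone who answered No to Question 2 can be read in the light of that answer. It does not help Questions 3 and 4. Question 2 asks about usefulness as a support, not about which domains were explored, and those two items have no free text.

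**An unticked option is itself negative information.** This holds for someone who ticked other options in the same list. It does not hold for someone who ticked nothing, and that is the case at issue.

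**The percentage base.** A reader might infer that percentages will be taken of all ticks. For instance, if 35 people each ticked 5 of 7 domains (175 ticks), a domain ticked by 25 people would read 25/175 = 14.3% instead of 25/35 = 71.4%. The analysis section does not say this. Its wording can equally mean the share of participants choosing each option. The base is undefined, not wrongly set, and may properly be fixed in an analysis plan that is not shown. It is no fault on its own.

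**Inflated percentages.** A reader might also infer that those who see no fit fall out of the base, so that every percentage is too high. Nothing in the document says that blanks are dropped, and the counts above are assumed.

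**Small consequences.** The survey is descriptive with no decision rule, and Limitations calls the evidence formative. This stands and limits the weight of the point. It does not remove it, because the change is easy now and impossible after data collection.

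**Conclusion.** The point holds as a gap in the survey form. As printed, Questions 3 and 4 cannot record that a participant saw no domain explored or was unsure, and a blank on either cannot be told apart from a skipped item. They are the only survey items for a construct defined as whether content aligns with the domains. Question 5 has the same gap in weaker form.

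The size of any bias cannot be derived from the document. The illustrative 57% against 67% rests on assumed counts (20 ticks, 5 blanks, 35 participants) and on multiple ticks and blanks being allowed; the larger differences in the table need more blanks. If an answer were forced, the effect would be a push towards positive ticks, which the document gives no means to quantify. The documents do not support the broader conclusions that the study shuts out negative views or that its percentages will be wrong.

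**What to change.** Before phase 3 data collection in June 2026:

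1. Add *None of these* and *Unsure* to Questions 3 and 4, each mutually exclusive with the listed domains and with each other.
2. Add the same two options to Question 5, for consistency with Question 2.
3. Report both as their own rows in the summary table, base percentages on participants who completed the survey, and show unanswered items separately.

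The cost is a few answer options in REDCap and a sentence of analysis text. The downside is that some percentages may look less favourable.
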